#### Secondary objectives

1) Explore and describe nurse-perceived changes in caring attitudes/behaviours post-intervention (T2); and 2) examine the mediating effects of team cohesion on quality of NPR and nurse QoWL.

#### Proposed hypotheses

Based on Duffy and Hoskins’ framework [9, 29] and in accordance with the main objectives of this research, we will make the following statistical hypotheses: 1) post-intervention, frequency of nurse caring attitudes/behaviours will be higher in the experimental group (EG) vs a waiting-list control group (WLCG); 2) post-intervention, team cohesion level will be higher in the EG vs the WLCG; 3) post-intervention, level of nurse QoWL will be higher in the EG vs the WLCG; 4) post-intervention, patient-perceived frequency of nurse caring attitudes/behaviours will be higher in the EG vs the WLCG; and 5) post-intervention, level of patient QoL will be higher in the EG vs the WLCG.

## Method

### Study design

Given the research questions and the intervention’s implementation in a natural setting, we will conduct a mixed-method cluster randomised controlled trial (RCT) [32] with a WLCG. This design allows collecting both quantitative and qualitative data [33]. However, given the aim and context of the study described in this protocol, the quantitative approach will dominate and the qualitative phenomenological approach will be enacted two months post-intervention (T2) to explore process and context factors encountered during the trial. We wish to obtain nurses’ perceptions regarding potential changes after the EI and of potential benefits. The reasons for going with this particular design are multiple. First, the choice of a cluster RCT over a classic RCT is called for given the high risk of contamination between control group and EG if the two are present in the same establishment [34]. Second, mixed-method data collection is recommended particularly when research questions have multiple facets and one method alone cannot serve to explore them all [33], which is the case with our study. Moreover, according to Hesse-Biber [32], incorporating qualitative data collection in a quantitative experimental research design can enhance the findings’ credibility. The choice of a WLCG, for its part, rests on three key factors. First, a higher inclusion rate can be reached if all HD units receive the intervention, whether immediately or one year later. Second, it allows diminishing bias related to prior acquaintance with patients. Third, from an ethical point of view, it seems appropriate for all of the participating nurses to receive the intervention, as it could be beneficial both to their QoWL and to the QoL of patients in their care.

Because of the nature of the EI, nurses cannot be blinded. Researchers are not blinded as well. Nevertheless, a separed group of researcher who are not involved in the EI will conduct data entry and analysis.

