### Data analysis

For the quantitative component of the study described in this protocol, first, we will check the data for inclusion conditions and outliers. Outlying data will be verified individually. Second, associations between factors and outcomes will be described using frequencies, means and standard deviations or medians and interquartile ranges. In addition, these associations will be evaluated using chi-square tests, Fisher tests or analyses of variance. Third, linear regression models adjusted for significant sociodemographic and health variables will be used to examine the intervention’s effect on the different variables selected for the study, keeping in mind that nurse QoWL remains the key outcome variable. Moreover, we will consider a random intercept to take HD unit variance into account. Fourth, we will test whether team cohesion acts as a mediator in the relationship between NPR (independent variable) and nurse QoWL (outcome variable). For this purpose, we will run three regressions: 1) regression of mediator on independent variable (EIIP-70); 2) regression of outcome variable (QoWL) on independent variable; and 3) regression of outcome variable on both independent variable and mediator. Fifth, an intention-to-treat analysis will be conducted of the data on all participants, whether they complete the intervention or not. This will diminish bias related to protocol deviations or withdrawals and will allow estimating the intervention’s effects under conditions that are close to real life. Sixth, based on sample size and sample design (10 HD units of different sizes for a total of 135 nurses) and considering an intra-class correlation coefficient of 0.03 for the HD units, we will be able to detect an effect size of 0.6, with statistical power of 0.8 and significance level at 0.05 for all analyses. The expected effect size has been fixed by the investigators and corresponds to the minimal clinically significant effect. The intra-class correlation coefficient selected is in line with Giraudeau’s recommendations [52] of 0.001 to 0.05 for a cluster RCT. The data will be analysed using the R software [54].

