### Ethical considerations

Special attention will be focused on three ethical elements: informed consent (of nurses and patients), confidentiality, and support. Regarding informed consent, the study participation form will provide information on the purpose of the study described in this protocol, the measures to be used to ensure anonymity, and freedom to withdraw from the study at any time without consequence for their professional career in the case of the nurses and for treatment and care received in the case of the patients. Consent forms completed by respondents will be kept in a suitable place for as long as required by the Swiss Ethics Committees on Research Involving Humans. Regarding confidentiality, the names of the respondents will not appear on any form or interview transcript. A code will be assigned to each form and a letter to each establishment. For the purposes of longitudinal follow-up, a password-protected file will be created containing the information necessary to administer questionnaires post-intervention. This file will be destroyed upon completion of the repeated measurement at twelve post-intervention. Regarding support, respondents will be able to reach a contact person throughout the study if they have any questions. They will also be able to access all the study results and/or a summary of the highlights by email, telephone, conventional post or the Moodle interface. The principal investigator will be responsible for drafting the final research report. Researchers have already obtained the required ethics certificate from the Human Research Ethics Review Board of the Canton of Vaud (Switzerland).

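### The data entry and analysis group is separated from the intervention but not stated to be masked to arm, so inclusion, outlier and covariate decisions can be taken with the arms in view

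*Protocol article*

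**What the plan says.** On blinding, the protocol article (Study design) gives the nature of the EI as the reason why nurses cannot be blinded. It then continues, without a reason and without an exception: "Researchers are not blinded as well. Nevertheless, a separed group of researcher who are not involved in the EI will conduct data entry". The sentence goes on to give the same group the analysis, and this separation is the only mitigation offered.

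On what the analysis stage involves, the Data analysis section begins: "first, we will check the data for inclusion conditions and outliers. Outlying data will be verified individually". No numerical rule for an outlier is given, nor the consequence of failing the inclusion check. The same section says that "linear regression models adjusted for significant sociodemographic and health variables will be used to examine the intervention’s effect", with a random intercept for haemodialysis unit, and it promises an intention-to-treat analysis of all participants whether or not they complete the intervention.

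On identifiers, Ethical considerations says: "A code will be assigned to each form and a letter to each establishment". It does not say that the link from letter to arm is withheld from anyone.

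**The concern.** Not delivering the intervention and not knowing the arm are different safeguards. The first removes a personal stake in the training sessions. The second prevents a decision about a record or a model from depending on the arm. The plan offers only the first.

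This matters more here than in many trials. The outcomes are questionnaire ratings by nurses and patients, nurses know their arm, and under Limitations data collectors read the questionnaires to patients. Little can be done about knowledge of arm at delivery or among the nurses who rate themselves. Data entry and analysis are among the few stages where arm-dependent decisions can still be prevented. If they are not, the effect estimate and its 0.05 test are exposed to choices made with sight of the arms, across five hypotheses and three post-intervention time points.

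**Working it through.** No arithmetic in the documents bears on masking, so the check sets the sections side by side.

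**1. Who is masked?** Nurses: no, with a reason. Researchers: no, without exception. Data entry and analysis group: described only by its separation from the EI. Read together, these sentences describe separation and stop short of masking.

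**2. What does that group decide after randomisation?** Study design assigns it data entry and analysis, so the steps under Data analysis fall to it:

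- who meets the inclusion conditions;
- what happens to outlying values, verified one by one;
- which sociodemographic and health variables count as significant and enter the model.

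**3. Does any of these need the arm?**

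- The inclusion criteria under Participants are largely factual, such as at least six months in the department for nurses, and age 18 or over with at least six months of treatment for patients. They can be checked without the arm.
- An outlying score can be verified against its form without the arm.
- Covariates can be chosen by their association with the outcome without the arm. The article does not define what significant refers to. On a file without the arm, only association with the outcome can be tested, which would settle that question.
- The random intercept needs a unit identifier, but a scrambled letter serves.

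The arm is first needed when the between-arm contrast is estimated.

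**4. Would recoding the arms as A and B be enough?** No. Swapping the labels turns the test statistic t into −t. The two-sided p-value depends on |t| and is unchanged. Someone holding an A/B file could still compare models by their p-values. The arm variable has to be absent from the file until the decisions are signed off.

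**5. Inclusion check against intention to treat.** Under Sampling procedure, units, nurses and patients are enrolled before randomisation. An inclusion check at the analysis stage is compatible with analysing all participants only if failing it does not remove anyone from the main analysis. The article does not say so.

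**6. Is there still time?** Preliminary results reports the first wave of data collection complete (140 patients, 100 nurses) and the EI delivered to all included EG nurses. Decisions for the post-intervention time points T1, T3 and T4 can still be locked.

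**7. Does the fix disturb the stated power?** The plan's inputs are "10 HD units of different sizes for a total of 135 nurses" and, "considering an intra-class correlation coefficient of 0.03 for the HD units", an effect size of 0.6 at power 0.8. With a mean of 135/10 = 13.5 nurses per unit and equal unit sizes, the design effect is 1 + (13.5 − 1) × 0.03 = 1.375. The effective total is 135/1.375 = 98.2, or 49.1 per arm at a 1:1 split. Power (normal approximation, two-sided 0.05) is Φ(0.6 × √(49.1/2) − 1.96) = Φ(1.01) = 0.84. Unit sizes are not given; if their coefficient of variation is assumed to be 0.65, the design effect is 1.546 and power is 0.80. The stated figure is thus reproducible under plausible sizes, and none of its inputs changes with masking.

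**The case against.** The strongest reply is that the article never says the data group knows the arms. It introduces that group as a safeguard, and procedures for masking analysts could sit in a full protocol or analysis plan not shown here. It is true that knowledge of arm is not stated outright. But the article does take a position on blinding: researchers are not blinded, with no exception. A later plan could fix outlier and covariate rules without undoing that sentence. If the group is in fact masked, one sentence in the article settles the point.

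Four stronger readings are tempting and not supported:

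- A reader might infer that the plan uses the nature of the EI to excuse unmasked analysts. It gives that reason for nurses only.
- A reader might infer that outliers or ineligible participants will be deleted. The text says verified and checked, and it commits to all participants. The gap is that removal is not ruled out.
- A reader might attach an inflated type I error to the lack of masking. Simulating a free choice among several covariate sets and outlier rules gives about 10% to 12% against a nominal 5%. Those rates rest on assumed covariates and cut-offs, and they measure unrestricted model choice. As step 4 shows, A/B labels alone would not change them, so they are not the effect of masking.
- A reader might call masking free. The random intercept requires unit identifiers, and ten units of unequal size may be recognised from their counts. The documents also do not say whether the person running the allocation in R is outside the group that analyses in R. The measure is cheap and its protection is partial.

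**Conclusion.** The point holds as a stated weakness in the design. The article declares researchers unblinded and offers separation from the EI in place of masking, while the analysis stage contains three decisions that need no knowledge of arm and could be taken with it. This rests on reading the unqualified statement about researchers as covering the data group, which is the natural reading but is not spelled out.

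The size of any bias cannot be derived from the documents, and none is claimed. The weakness does not invalidate the trial. It is an avoidable exposure of the main estimate, worth correcting while decisions for T1, T3 and T4 remain open.

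**What to change.** Add to Study design:

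1. The data entry and analysis group works on a file without the arm variable and with re-scrambled unit letters. The key is held by someone outside that group.
2. Inclusion, outlier and covariate or model decisions for T1, T3 and T4 are signed off on that file before any between-arm comparison is run and before the key is released.
3. All randomised participants stay in the main analysis, in line with the intention-to-treat statement under Data analysis. Anyone failing the inclusion check is removed only in a sensitivity analysis.

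The cost is a paragraph of text, a recoded file, a sign-off step and a named key-holder independent of the analysis. Sample size and conduct at the sites do not change. Because some units or arms may still be guessed, the sign-off before any comparison carries most of the protection and should not be dropped in favour of recoding alone.

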### Participants

The studied population is twofold: nurses working in HD units and HD patients in direct contact with these nurses. The nurse population will consist of all nurses working in the HD departments of ten hospitals in the French-Swiss cantons included in the study described in this protocol. This corresponds to an accessible population of 135 nurses. The inclusion criteria will be the same as in the Quebec pilot study [6]: 1) at least 6 months’ work experience in the department; and 2) consent to take part in the study. In addition, nurses who intend to leave the HD unit within three months will be excluded. The patient population will consist of the patients at the HD units participating in the study. This corresponds to an accessible population of 430 patients. Their inclusion criteria will be the following: 1) at least 18 years of age and under active treatment for at least six months; 2) fluency in French; and 3) capacity to provide informed consent. Their exclusion criteria will be the following: 1) diagnosed with dementia; and 2) new to the HD unit. In this regard, six months will be the minimum required period of exposure to the team. As care teams are generally well acquainted with the patients in their care, they will be asked to help with recruitment in order to avoid soliciting patients unable to provide consent and to ensure inclusion criteria are met. Exclusion criteria will be reduced to a minimum to avoid patients feeling snubbed by the care team. Based on past experience, the average participation rate among HD patients is approximately 50% of those who meet the inclusion criteria [25, 35].

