Against this background and with a view to reviving nursing humanistic practices in care settings, an educational intervention (EI) was developed in Quebec [18, 19] on the basis of Watson’s Theory of Human Caring [20, 21]. The intervention was implemented and evaluated in two pilot studies, first, qualitatively in a population of rehabilitation nurses in Quebec [19] and, then, with mixed methods in a population of HD nurses in French Switzerland [22]. The choice of these two populations rested on the fact that nurse presence and quality of nurse-patient interactions play a key role in patient QoL [23, 24]. Both studies [19, 22] showed that the EI had a high acceptability and feasibility level. Furthermore, a secondary qualitative analysis of the two pilot studies [25] showed that results converged in large part regarding the intervention’s feasibility, acceptability and benefits for nursing practice. This convergence justifies the implementation now of a large-scale experimental study [26, 27] to test the effects of the EI on various outcome variables, including quality of working life (QoWL) of nurses, QoL of patients in their care, and quality of NPR.

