### Sampling procedure

For the quantitative component of the study described in this protocol, a cluster will be composed of the nurses and patients of a HD department. The HD units of every hospital in French Switzerland will be contacted to take part in the study, for a total of 13 units. To date, 10 units have already expressed their desire to take part in the study: Centre Hospitalier Universitaire Vaudois (Lausanne), Ensemble Hospitalier de la Côte (Morge), Établissements Hospitaliers du Nord Vaudois (Yverdon), Hôpital du Valais (three independent sites in Sion, Sierre, and Martigny), Hôpital du Jura (Delémont and Porrentruy), Hôpital Intercantonal de la Broye (Payerne), Hôpital Riviera-Chablais (Monthey), Hôpitaux Universitaires de Genève (Geneva).

Once the HD units and all the nurses and patients that compose them are enrolled, they will be randomised by computer to the EG or the WLCG. Among the 1024 (=2^10^) possible allocations to EG and WLCG, we will limit our choices to those where both the EG and the WLCG contain at least 50 nurses. Under this constraint, there are still 410 possible allocations and the number of units per group ranges from 2 to 8. The R software (version 3.3.0) [36] will be used to choose an allocation at random from among these 410 possibilities. All units will have the same probability of being included in the EG.

For the qualitative component, a purposive sample will be used. This sampling method allows selecting persons that have lived the experience under study (in our case, participation in the EI) and that agree to share it. It is best with this method to recruit a wide variety of participants in order to collect as diverse a set of viewpoints as possible on the phenomenon under study. Participants for this component will be selected from among the EG nurses. Moreover, in order to take account of staff heterogeneity across EG units, the number of participants invited to be interviewed will be weighted based on unit size. It is difficult with qualitative approaches to determine beforehand the number of participants required. Benner [37] recommends 5 to 25 but specifies that it is necessary to keep interviewing until the discourse becomes redundant, that is, until adding participants to the sample and more data to those already collected sheds no more light on the phenomenon under study [38]. Based on the experience of researchers in the field, it is estimated that a sample of 18 participants will be required.

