### HD nurses

#### Sociodemographic data

At pre-test (T0), personal data (sex, age) and work-related information (employment status, years of experience as HD nurse, number of patients attended to per work shift) will be collected.

The nurse-patient relationship (NPR) will be measured with the French-language version (EIIP-70) [39] of the Caring Nurse-Patient Interaction Scale (CNPI-70). This tool comprises 70 items covering 10 dimensions that capture each of Watson’s 10 CF. It allows nurses to self-rate their frequency of caring attitudes/behaviours. The dimensions covered by the instrument are the following [39]: humanism (6 items), hope (7 items), sensitivity (6 items), relationship (7 items), emotions (6 items), problem solving (6 items), teaching (11 items), assistance (10 items), and existential factors (6 items). Respondents must choose from five responses ranging from 1 (almost never) to 5 (almost always). This tool was validated on 377 nursing students and demonstrated good psychometric properties (range of Cronbach’s alphas for the 10 sub-dimensions of 0.73 to 0.91) [39]. Moreover, the two pilot studies showed respondents had no difficulty understanding the questionnaire and completing all the questions.

Team cohesion will be measured with the Group Environment Questionnaire (GEQ) [40] adapted for work teams [41]. A French-language version of the questionnaire was created following the back-translation procedure [41]. Like the original, the French-language version comprises 18 items and encompasses the four dimensions of team cohesion [42], namely, respondent social-related attraction to group (five items, one of which is reverse scored), respondent task-related attraction to group (four items, two of which are reverse scored), social-related group integration as perceived by respondent (four items, two of which are reverse scored), and task-related group integration as perceived by respondent (five items, one of which is reverse scored). The response scale ranges from 1 (strongly disagree) to 5 (strongly agree). The questionnaire was tested on a sample of nurses from another healthcare institution. No major comprehension difficulties emerged. Cronbach’s alphas for the different dimensions ran from 0.71 to 0.81 [41].

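### The nurse criteria are silent on prior receipt of this intervention in the French-Swiss pilot, so already-trained nurses could enter the waiting-list control group

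*Protocol article*

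**What the plan says.** The Background section of the protocol article reports that the educational intervention (EI) has been piloted twice. The second pilot was run "with mixed methods in a population of HD nurses in French Switzerland".

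Under Sampling procedure, the trial draws on the same region: "The HD units of every hospital in French Switzerland will be contacted to take part in the study, for a total of 13 units". Ten units had agreed. No unit is set aside for having hosted the pilot. The one restriction on allocation is "we will limit our choices to those where both the EG and the WLCG contain at least 50 nurses", and every unit has the same chance of either arm.

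Under Participants, "The nurse population will consist of all nurses working in the HD departments of ten hospitals in the French-Swiss cantons". The inclusion criteria, taken from the Quebec pilot, are "at least 6 months’ work experience in the department; and 2) consent to take part in the study". One exclusion is added: "In addition, nurses who intend to leave the HD unit within three months will be excluded".

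The baseline nurse data are sex and age, plus "work-related information (employment status, years of experience as HD nurse, number of patients attended to per work shift) will be collected". Earlier training in the EI is not among them.

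**The concern.** The trial contrasts nurses who receive the EI with nurses who have not yet received it. A site applying the criteria as written would enrol a pilot-trained nurse as if she were untreated. If her unit is allocated to the waiting-list control group (WLCG), she is a treated control, and the difference between the arms is understated for every nurse outcome the EI affects. The Study design section chooses cluster randomisation to avoid contamination of the control arm within an establishment. A pilot unit in the WLCG would bring contamination in by another route.

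Two features make this more than a stray nurse or two. Pilot participants would probably be concentrated in few units, so chance allocation could put most of them in one arm. And because prior receipt is not among the listed baseline items, the adjusted regression in Data analysis has no listed variable with which to account for it. The intention-to-treat principle does not help, since it keeps these nurses in the arm to which they were allocated.

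**Working it through.** **Inputs from the article**
- 10 units and 135 nurses, so mean unit size m = 135/10 = 13.5 (Data analysis).
- Intra-class correlation 0.03, effect size 0.6, power 0.80, significance level 0.05 (Data analysis). Sidedness is not stated; two-sided is assumed.
- At least 50 nurses per arm (Sampling procedure).

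**Assumptions, because the article gives no figure**
- k = 5 or 10 pilot-trained nurses, all in the WLCG.
- The pilot effect is fully kept.
- Equal arms of 135/2 = 67.5.
- Coefficient of variation (CV) of unit size 0, with 0.6 as an alternative.

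**Step 1: reproduce the plan's power**
- Design effect = 1 + ((1 + CV²)m − 1) × 0.03. At CV 0 this is 1 + 12.5 × 0.03 = 1.375.
- Standard error in SD units = √(1.375 × 2/67.5) = 0.202.
- Power = Φ(0.6/0.202 − 1.96) = 0.844.
- At CV 0.6 the design effect is 1.521 and power is 0.807.

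The stated 0.80 is therefore reproduced for moderately unequal units. That figure is not in dispute here.

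**Step 2: dilute the control arm**

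Expected contrast = 0.6 × (1 − k/67.5).

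| k | Treated share of WLCG | Contrast (SD) | Power, CV 0 | Power, CV 0.6 |
|---|---|---|---|---|
| 0 | 0% | 0.60 | 0.844 | 0.807 |
| 5 | 7.4% | 0.556 | 0.786 | 0.744 |
| 10 | 14.8% | 0.511 | 0.716 | 0.673 |

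If only half of the k nurses fall in the WLCG, power at CV 0 is 0.817 (k = 5) or 0.786 (k = 10).

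If the WLCG is at the 50-nurse floor, with 85 in the other arm, the contrast is 0.6 × (1 − 5/50) = 0.54 to 0.6 × (1 − 10/50) = 0.48. Power at CV 0 then falls from 0.819 to 0.734 and 0.632.

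**Step 3: leave the k nurses out instead**

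With N = 135 − k and the effect back at 0.6, power at CV 0 is 0.835 (k = 5) or 0.824 (k = 10). At CV 0.6 it is 0.797 or 0.787. The cost against Step 1 is about 1 to 2 points.

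**Step 4: exposure in the experimental group (EG)**

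The Proposed hypotheses compare post-intervention levels between arms. The adjustment in Data analysis names sociodemographic and health variables, not baseline outcome values. On that contrast, a pilot-trained EG nurse who keeps the effect does not reduce the difference. She would reduce it only in a change-from-baseline or baseline-adjusted comparison, because she starts higher and has less to gain.

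**The case against.** The strongest reply is that the harm depends on facts the article does not give: where the pilot took place, how many nurses were trained, and whether they still work in a participating unit. Three of the 13 units had not joined, and the pilot unit could be one of them. This stands. A reader might infer that the comparator is in fact contaminated, or that colleagues and patients of pilot nurses have been exposed. The article supports neither statement; it shows only that nothing in the criteria prevents it.

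A reader might also infer that prior exposure in either arm shrinks the effect. Step 4 shows that this does not hold for the post-intervention contrast the protocol describes. The arm rule is symmetric and the units have equal probabilities, so a single participating pilot unit is as likely to fall in the EG as in the WLCG.

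Much larger losses can be constructed. Fifteen trained nurses in a WLCG of 37 (50 × 100/135, using the first-wave count of 100 nurses) would be 15/37 = 41% treated, leaving about 0.36 SD. That combines a count above the mean unit size of 13.5, an arm below the 50-nurse floor, every trained nurse in the WLCG, and full retention of the effect. It should not be used as a planning figure.

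Two smaller replies also have force. The questionnaire itself is not shown, so prior receipt is only known to be absent from the listed items. And baseline outcome levels are measured, so a raised starting level might be visible by unit; it could not, however, be attributed to the pilot without knowing who was trained.

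None of this closes the gap. Eligibility belongs in the protocol rather than the analysis plan, and the article states the nurse criteria as a list.

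**Conclusion.** The criteria have a real gap: as written they admit nurses who have already had the EI, in the region where it was piloted. The consequence is possible, not demonstrated. Under the assumptions in the working, 5 to 10 trained nurses in the WLCG would cost about 0.04 to 0.09 SD of a 0.6 SD effect, and about 6 to 13 power points with equal unit sizes. The loss is smaller if the pilot effect has faded or the nurses are split between arms, larger if the WLCG is at its minimum size, and zero if no pilot nurse is enrolled. The point merits action because the remedy costs much less than the loss it guards against.

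**What to change.** - For any nurse still to be enrolled, add previous receipt of this EI to the exclusion criteria.
- For nurses already enrolled, establish prior receipt from the pilot's records, if the team holds them, or by one question. Report the count by arm and unit. If it is zero, one sentence saying so settles the matter.
- Before any outcome analysis, pre-specify a nurse analysis that leaves out previously exposed nurses by the same rule in both arms, reported beside the intention-to-treat result. Prior receipt in the pilot is fixed before randomisation, so this does not select on anything the allocation could have influenced.
- If a participating unit hosted the pilot, add a matching patient sensitivity analysis without that unit. This also addresses carry-over to untrained colleagues, which dropping individual nurses does not.

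Preliminary results reports that the first data wave is complete and the EI has been delivered to all EG nurses. A companion analysis is therefore more suitable than redefining the main comparison. The cost is one criterion, one question or records check, and the extra analyses. Precision falls slightly in the nurse analysis, and the patient sensitivity analysis loses one of ten clusters.
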